# Performance feedback on the quality of care in hospitals performing thrombectomy for ischemic stroke (PERFEQTOS): protocol of a stepped wedge cluster randomized trial

**DOI:** 10.1186/s13063-021-05819-z

**Published:** 2021-12-04

**Keywords:** Performance feedback, Endovascular thrombectomy, Stepped wedge cluster randomized trial, Ischemic stroke, Quality of care

## Abstract

**Background:**

Although the provision of performance feedback to healthcare professionals based on data from quality registries is common practice in many fields of medicine, observational studies of its effect on the quality of care have shown mixed results. The objective of this study is to evaluate the effect of performance feedback on the quality of care for acute ischemic stroke.

**Methods:**

PERFEQTOS is a stepped wedge cluster randomized trial in 13 hospitals in the Netherlands providing endovascular thrombectomy for ischemic stroke. The primary outcome is the hospital’s door-to-groin time. The study starts with a 6-month period in which none of the hospitals receives the performance feedback intervention. Subsequently, every 6 months, three or four hospitals are randomized to cross over from the control to the intervention conditions, until all hospitals receive the feedback intervention. The feedback intervention consists of a dashboard with quarterly reports on patient characteristics, structure, process, and outcome indicators related to patients with ischemic stroke treated with endovascular thrombectomy. Hospitals can compare their present performance with their own performance in the past and with other hospitals. The performance feedback is provided to local quality improvement teams in each hospital, who define their own targets on specific indicators and develop performance improvement plans. The impact of the performance feedback and improvement plans will be evaluated by comparing the primary outcome before and after the intervention.

**Discussion:**

This study will provide evidence on the effectiveness of performance feedback to healthcare providers. The results will be actively disseminated through peer-reviewed journals, conference presentations, and various stakeholder engagement activities.

**Trial registration:**

Netherlands Trial Register NL9090. Registered on December 3, 2020

**Supplementary Information:**

The online version contains supplementary material available at 10.1186/s13063-021-05819-z.

## Introduction

### Background and rationale

In 2019, more than 30,000 ischemic stroke patients were admitted to Dutch hospitals and this number is increasing every year [1]. Ischemic stroke is a major cause of death and long-term disability [2]. Randomized trials showed that early endovascular thrombectomy (EVT) substantially improves the 3-month functional outcome with an absolute risk reduction in terms of death or permanent disability of 19.5% [3–5]. With EVT, the neuro-interventionalist advances a catheter through the femoral artery up to the occluded cerebral artery to remove the occlusion of blood clots. The effectiveness of EVT is highly time-dependent. Every hour delay in the initiation of EVT results in death or permanent disability in 1 out of every 19 patients [6]. Several trials and observational studies noted an association between an efficient workflow to achieve fast recanalization and a stronger treatment effect of EVT resulting in better clinical outcomes [7–11]. Therefore, having the right infrastructure and an efficient process of care is of utmost importance to be able to treat every patient as fast as possible.

Performance feedback has been defined as “a summary of clinical performance on a specific indicator, e.g. process measure, with benchmarking against performance of other providers over a specified period of time with or without recommendations for action” [12–15]. Providing performance feedback regarding process indicators to healthcare professionals has become quite common in healthcare [12, 16]. However, performance feedback has no firm empirical basis and consensus on how this feedback is best to be provided is lacking [12]. A Cochrane systematic review of 140 studies on the effectiveness of audit and performance feedback on the quality of care reported a median 4.3% absolute improvement in patient outcomes (interquartile range 0.5–16%) [12]. However, effects tend to be very heterogeneous, and success factors for the design and delivery of effective performance feedback have not been identified. Understanding heterogeneity of effect has been limited in part by the lack of appropriate design of the feedback interventions and the absence of a quantitative evaluation of effectiveness [17–20]. The aim of this study is to evaluate the effect of providing performance feedback to healthcare providers in individual EVT hospitals to improve the quality of stroke care.

### Objectives

Since stroke logistics and time metrics vary considerably between centers and within centers, and are strongly associated with outcome [21], this study aims to assess the extent to which performance feedback to healthcare providers in individual hospitals providing EVT for ischemic stroke, resulting in action plans and targets based on this feedback, reduces time from arrival at the hospital to initiation of EVT and thereby improves the quality of care.

## Methods

### Trial design

We designed a stepped wedge cluster randomized trial (CRT) of performance feedback on the quality of care in hospitals performing EVT for ischemic stroke (PERFEQTOS) to determine the impact of a performance feedback intervention accompanying hospital-specific action plans and improvement targets. This is a specific form of CRT in which initially all clusters (in this study: hospitals) serve as controls. The intervention is rolled out sequentially but randomly at different time points, such that at the end of the study all clusters have crossed over to the intervention condition (Fig. 1) [22]. In the present study, the design includes an initial 6-month period in which none of the hospitals receives performance feedback. Subsequently, every 6 months, three or four randomly chosen hospitals will cross over from control to intervention conditions, which implies a total study duration of 30 months given that 13 hospitals participate. The Standard Protocol Items: Recommendation for Interventional Trials (SPIRIT) checklist [23] is shown in Additional file 1.

**Fig. 1 Fig1:**
[figure not shown]
SPIRIT figure. Schematic visualization of stepped wedge cluster randomized trial control and intervention allocation, follow-up, and reporting of the study

### Study setting and participants

The study will be carried out in specialized neuro-intervention hospitals performing EVT for ischemic stroke. In the Netherlands, EVT is concentrated in 17 such specialized hospitals [24]. All EVT hospitals are invited to participate in this trial with no specific inclusion or exclusion criteria. Thirteen out of these 17 hospitals agreed to participate in the study (Fig. 2). The participating hospitals include all admitted adult patients with acute ischemic stroke who underwent EVT.

**Fig. 2 Fig2:**
[figure not shown]
Specialized EVT hospitals in the Netherlands which participate in this study

### Randomization and intervention allocation

Randomization will be performed according to a lottery method of sampling by the Study Coordinator in the presence of the Principal Investigator and an independent observer and will be videotaped. Once the hospitals provided consent to participate in the study, each enrolled hospital will start in the control condition. Every 6 months, three to four hospitals will be randomized to cross over to the intervention condition. All other hospitals stay in the control condition. This procedure continues every 6 months until all hospitals are crossed over to the intervention condition. Participating hospitals will be blinded to the allocation sequence, and those hospitals not yet in the intervention condition will not be aware of the time at which they will cross over to the intervention condition. When a hospital is crossed over to the intervention, this is communicated to all participating hospitals.

### Intervention

#### Dashboard design

When it comes to performance feedback, it is necessary to visualize and communicate the information content in such a way that care providers can use this information for improvement and to maximally reduce the risk of misinterpretation of the results [25]. With this in mind, we developed a dashboard containing quality of care measures per hospital, benchmarked against the average/median performance of the other hospitals for the same time period as well as their own performance over time. Prior to designing this dashboard, we reviewed the general empirical literature on dashboard design [25–32]. Based on the insights from previous studies, we composed a dashboard containing a compositional qualitative and quantitative (graphical display with textual explanation) visualization of quality of care data. Specifically, the PERFEQTOS dashboard provides an overview of results on quality of care indicators and patient characteristics (Fig. 3). The performance feedback is presented in a way that clearly highlights the key message (i.e., improvement is recommended or not), limiting the amount of extra information to increase actionability while still allowing the recipient hospital to view more detailed comparative information.

**Fig. 3 Fig3:**
[figure not shown]
Screenshots of the PERFEQTOS dashboard (generated from anonymous data)

### Indicator measurement for the dashboard

Evaluation of healthcare providers’ quality performance is commonly done using a combination of structure, process, and outcome indicators (Table 1) [33, 34]. Our dashboard follows that approach.

**Table 1 Tab1:** Quality of care indicators included in the dashboard

Quality indicators	Type	Definition
Center volume	Structure	The total number of patients treated with EVT in each individual hospital
Number of transferred patients	Structure	Whether patient transferred from another hospital to an EVT hospital
Door-to-needle time	Process	Time from arrival at the emergency department of EVT hospital to IVT initiation
Door-to-groin time	Process	Time from arrival at the emergency department of EVT hospital to groin puncture
eTICI	Outcome	Thrombolysis in cerebral infarction scale to assess intracranial reperfusion, ranging from 0 (no reperfusion) to 3 (full reperfusion)
NIHSS at 24 h	Outcome	The neurological deficit ranged between 0 (normal function) and 42 (completely impaired)
mRS at 3 months	Outcome	Functional outcome score of mRS evaluated 3 months after EVT treatment ranged between 0 (no symptom) and 6 (death)

*eTICI* extended thrombolysis in cerebral infarction, *NIHSS* National Institute of Health Stroke Scale, *mRS* modified Rankin Scale, *EVT* endovascular thrombectomy, *IVT* intravenous thrombolytics

Structure indicators are the total number of patients treated with EVT in each hospital (henceforth referred to as “center volume”), the number of direct (i.e., non-transferred) and transferred stroke patients from other hospitals, and completeness of data.

Process indicators are time from arrival at the emergency department of the intervention hospital to start of the intravenous thrombolytics (IVT) administration (door-to-needle time) for non-transferred patients and time from arrival at the emergency department of the intervention hospital to initiation of EVT (door-to-groin time) for all patients. In case a patient has an ischemic stroke while already admitted to the hospital, then the arrival time is defined as the time the neurologist first assessed the patient. We stratified the indicators by whether patients are transferred or non-transferred from another hospital.

Outcome indicators are post-EVT reperfusion grade of the Extended Thrombolysis in Cerebral Infarction (eTICI) score, ranging from 0 (no reperfusion) to 3 (full reperfusion), and the National Institute of Health Stroke Scale (NIHSS) score at 24 h (± 12 h), which quantifies the neurological deficit caused by a stroke (range 0–42). In addition, the modified Rankin Scale (mRS) score is used as a measure of patients’ functional outcome after acute ischemic stroke, ranging from 0 (no symptoms) to 6 (death). The mRS score is assessed 3 months after admission. Since the outcome is strongly associated with baseline patient characteristics [35], patients’ age, sex, NIHSS score on arrival, location of the proximal intracranial occlusion, and time from onset to arrival at the intervention hospital (onset-to-door time) are also collected. Stroke onset is defined as the time point when stroke symptoms were first noticed by the patient or an observer. In cases the time of first symptoms is unknown, onset is defined as the moment the patient was last seen well. Additionally, we adjusted the outcomes per hospital for differences in these baseline characteristics.

### Strategy for quality improvement

The performance improvement cycle is depicted in Fig. 4 to reflect the procedures through which hospitals aim to improve their clinical performance. Each hospital randomized to the intervention will install a local quality improvement team. This team consists at least of a neurologist, an interventionalist, a resident in neurology, and a (stroke) nurse. It can be expanded with representatives of other relevant disciplines. Each quality improvement team is trained by one of the PERFEQTOS investigators to explain the dashboard functionalities, interpretation of data, and how action plans can be developed. Quality improvement teams of hospitals in the intervention cluster periods receive quarterly performance feedback reports, which they can use to set improvement targets pertaining to specific indicators and develop performance improvement plans to achieve those targets. The assumption is that if a center’s performance is below that of the comparator, an improvement target will be set accordingly, and subsequent improvement actions would be aimed at reaching the target and remove the discrepancy [16, 36, 37]. The impact of these actions can then be evaluated based on the next feedback report(s).

**Fig. 4 Fig4:**
[figure not shown]
The performance feedback cycle to improve each hospital’s performance. Adapted from Carver and Scheier’s Control Theory [36]

In addition, during workshops organized every 6 months for those hospitals randomized to the intervention, both the best performing hospital and most improved hospital share their best practices with the other hospitals.

### Data collection and management

Data on performance indicators and patient characteristics are routinely collected in each hospital and reported to the Dutch Acute Stroke Audit (DASA) from the Dutch Institute of Clinical Auditing (DICA). DASA is the main prospective clinical auditing tool for stroke in The Netherlands since 2014, with the aim to assure the quality of patient care and to aid in improving outcomes [38]. DICA is an independent organization, founded by medical specialists, that facilitates national audits for various medical professions, including the DASA. Hospitals are free to decide who carries out the data registration (e.g., nurses, data managers, neurologists), but the final responsible person is a neurologist. Medical Research Data Management (MRDM) processor, a trusted third party, is involved to pseudonymize the data to comply with privacy legislation. Hospitals can provide the collected data to MRDM in three ways. First, an online survey through a secured web environment is available for hospitals to record the data. Second, hospitals can provide the data in batches, i.e., data files in which large amounts of data can be transferred directly to MRDM. Third, to minimize the registration burden, some hospitals took the initiative to implement data linkage, i.e., extracting the data from their individual electronic patient health record to be automatically forwarded to MRDM [38]. Participating hospitals approved with a written agreement that MRDM send pseudo raw data about the patients treated in their hospital to the PERFEQTOS Study Coordinator at Erasmus MC. The Study Coordinator then aggregates the data into hospital-level medians and percentages. Data collection continues throughout the study, so each hospital contributes to both control and intervention cluster periods, which will be compared. Next, the aggregated data are summarized in a report and fed back via the dashboard. All hospitals randomized to the intervention group will receive a performance feedback report on a quarterly basis and will start and re-iterate the performance improvement cycle (Fig. 4).

### Study outcomes

The primary outcome is door-to-groin time. Secondary outcomes are door-to-needle time, eTICI score, NIHSS at 24 h, and mRS at 3 months (Table 1). These outcomes are collected for every individual patient (Table 1).

### Power calculation

The power calculation was based on mean differences in door-to-groin time as a primary outcome. We used a parametric power estimation methodology for stepped wedge designs put forward by Hemming and Girling [39] in the Stata function stepped wedge, derived from Hussy and Hughes [40]. We assumed 13 EVT centers were randomized in four clusters per time step (three clusters of three hospitals and one cluster of four hospitals) that treated an average of 30 patients per center per time period of 3 months [21]. We used a mean door-to-groin time of 77 min (standard deviation 47 min) and *ICC* 0.37, both obtained from the MR CLEAN Registry data [21, 24]. Assuming a significance level of 5%, this would result in 88% power to detect a clinically relevant reduction of door-to-groin time of 10 min.

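### The stated 88% power does not follow from the stated inputs, which give about 99.5%; a value near 88% arises if 30 patients are entered per 6-month step instead of per 3 months

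*Protocol article*

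**What the plan says.** The Power calculation section uses a stepped-wedge method derived from Hussey and Hughes. It takes 13 centers in four groups, three groups of three and one of four. Its volume assumption is that each center "treated an average of 30 patients per center per time period of 3 months". For the outcome it says: "We used a mean door-to-groin time of 77 min (standard deviation 47 min" and an ICC of "0.37, both obtained from the MR CLEAN Registry data". At a 5% significance level, "this would result in 88% power to detect a clinically relevant reduction of door-to-groin time of 10 min".

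The Trial design section sets the calendar: an initial 6-month control period, after which "every 6 months, three or four randomly chosen hospitals will cross over from control to intervention conditions", for 30 months in total.

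**The concern.** The volume is given per 3 months, but the steps are 6 months long. Thirty patients per 3 months is 60 per hospital per step period, or 13 × 60 × 5 = 3,900 patients over the trial. Thirty per 6 months would be half that, 1,950. With an ICC as high as 0.37, a stepped wedge relies mainly on within-hospital comparisons, and 60 patients per cell should give far more than 88% power for 10 min.

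This is the only sample-size justification in the article. If the volume is as stated, the trial can detect clearly less than 10 min. If the power is roughly as stated, the stated volume is too large by a factor of about two. A reader cannot tell which trial is described.

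**Working it through.** **Inputs.** From Power calculation: I = 13 hospitals (3/3/3/4), 30 patients per hospital per 3 months, total SD 47, ICC 0.37, difference 10 min, 5% level (taken as two-sided; the article does not say). From Trial design: T = 5 periods of 6 months, with crossovers at the start of periods 2 to 5.

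**Variance components.** 47² = 2209. Between hospitals: τ² = 0.37 × 2209 = 817.3. Within hospitals: σ² = 0.63 × 2209 = 1391.7.

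**Formula (Hussey-Hughes).** With s = σ²/m for m patients per hospital-period,

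Var = I·s·(s + T·τ²) / [(I·U − W)·s + (U² + I·T·U − T·W − I·V)·τ²],

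where U is the number of exposed hospital-periods, W the sum of squared period totals and V the sum of squared hospital totals. Power = Φ(10/SE − 1.96).

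**Attempt to reproduce 88% from the stated inputs (group of four last).**
- U = 12 + 9 + 6 + 4 = 31; W = 3² + 6² + 9² + 13² = 295; V = 3·16 + 3·9 + 3·4 + 4·1 = 91.
- I·U − W = 403 − 295 = 108. The τ² coefficient is 961 + 2015 − 1475 − 1183 = 318.
- m = 60: s = 23.19. Var = 13 × 23.19 × (23.19 + 4086.7) / (108 × 23.19 + 318 × 817.3) = 4.72, so SE = 2.173.
- Power = Φ(4.60 − 1.96) = Φ(2.64) = 99.6%. With the group of four at a middle step, SE = 2.194 and power is 99.5%.
- Detectable difference at 88% power: (1.96 + 1.175) × 2.173 = 6.8 min (6.9 min with SE 2.194).

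The printed 88% is not reproduced.

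**Other readings that keep the stated patient flow.**

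| Reading | Power |
|---|---|
| Ten 3-month periods of 30 | 99.6% (same SE, 2.173) |
| One-sided 5% | 99.8% |
| SD 47 read as within-hospital SD | 95.1% to 95.5% |
| t reference with 11 df | 98.2% to 98.7% |
| 12 hospitals × 60 | 99.3% |

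None is near 88%.

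**30 patients per 6-month period (s = 46.39).**
- 13 hospitals: SE = 3.067, power Φ(3.26 − 1.96) = 90.3%. With the group of four in the middle, SE = 3.098 and power is 89.8%.
- 12 hospitals, three per step: U = 30, W = 270, V = 90, coefficients 90 and 270; SE = 3.199, power Φ(3.126 − 1.96) = 87.8%.

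The gap therefore comes from 30 versus 60 patients per period. Removing one hospital at 60 per period lowers power only to 99.3%.

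**Sensitivity to an assumption built into the method.** The formula takes each hospital's mean as constant apart from the common time effect, that is, a cluster autocorrelation (CAC) of 1. For an assumed CAC, replace s by s + (1 − CAC)·τ² and τ² by CAC·τ². For 13 × 60:
- CAC 0.95: s = 23.19 + 40.87 = 64.06, τ² = 776.5, SE = 3.60, power 79%.
- CAC 0.90: s = 104.9, τ² = 735.6, SE = 4.59, power 59%.

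The article gives no value for the CAC; these are illustrations.

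**The case against.** Four points can be made for the plan.

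- **The error is on the safe side.** On the stated model, power is understated. The 13 hospitals are those of 17 that agreed to take part, and all their adult EVT patients are included, so the figure sets no recruitment target and nothing in conduct or analysis depends on it. This stands. It limits the consequence but does not make the figure correct.
- **Other routes lead to about 88%.** Thirteen hospitals with 28 patients per period give 88.3%, and 13 × 60 with a CAC of 0.97 gives 89.5%. This also stands. A reader might infer from the 87.8% match that only 12 hospitals were entered and one was left out. The article does not support that: it states 13 hospitals and the 3/3/3/4 split, and the match is not unique.
- **Power and analysis models agree.** Both the cited method and the model under Statistical methods have a single random effect for hospital, so a CAC of 1 is consistent within the plan. A reader might infer from the CAC figures that 88% is really too high. The documents do not support that either, because they give no between-period correlation. The Objectives section does mention variation in time metrics within centers, and the Discussion mentions heterogeneous improvement policies in the control phase. That makes the sensitivity analysis worth showing but supplies no value for it.
- **The 88% may be nearly right and the 3-month interval wrong.** This is possible. The volume is attributed to a cited source that is not available here, so the article alone cannot settle it.

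**Conclusion.** The point holds as an inconsistency in the stated figures. Under the cited method with two-sided 5% and SD 47 as the total SD, the stated inputs give 99.5% to 99.6% power, not 88%. The least favourable reading tried that keeps the stated flow and a CAC of 1 (SD 47 as within-hospital SD) still gives about 95%. Entering 30 patients per 6-month step gives 87.8% to 90.3%, which makes a mismatch between volume and period length the likeliest explanation, though not a proven one. Which inputs were used cannot be told from the article. The finding does not show that the trial is underpowered.

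**What to change.** First confirm two facts: the expected number of patients per hospital per 6-month period, and the number of hospitals entered in the calculation. Then restate the paragraph:

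- if the volume is 60 per 6-month period, about 99.5% power for 10 min, or a detectable difference of 6.8 to 6.9 min at 88% power;
- if the volume is 30 per 6-month period, correct the 3-month interval and state about 90% for 13 hospitals.

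In either case state the sidedness of the test, whether SD 47 is the total SD, and that the calculation assumes a CAC of 1. If a lower CAC was in fact entered, give it. Optionally, add power under hospital-by-period variation, labelled as assumed (for 13 × 60, about 79% at CAC 0.95 and 59% at CAC 0.90).

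The cost is one rewritten paragraph and a short recalculation. No design change or additional patients are needed.
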